### Procedures and study instruments

Names of eligible patients with their registration number of the electronic patient file (EPD) are provided by the diagnosing psychiatrists to the research assistant, who will make a first check on inclusion and exclusion criteria, informs the participants and asks them to join the study. Written informed consent will be obtained according to prevailing legal requirements before the start of the study. Eligible patients, HDRS ≥ 14 as primary outcome measure, perform the Åstrand submaximal cycling test, physical measures and fill out the questionnaire, after which the participants are randomized. All outcome parameters measured during baseline will be repeated three, six and 12 months after baseline, except for the blood samples (only at T0 and T6). Height is measured according to protocol (Seca 214, Hamburg, Germany) and a bio-impedance scale is used to measure weight and body composition (Omron HBF-510, Omron Healthcare Europe BV, The Netherlands). Waist circumference is measured twice with a tape measure (Seca 201, Hamburg, Germany) at the midpoint between the lower border of the ribs and the upper border of the pelvis. Systolic and diastolic blood pressure are registered twice at rest, using an electronic blood pressure meter (Omron M6 comfort, Omron Healthcare Europe BV, The Netherlands) with an adequate cuff size. Grip-strength is tested according to protocol using a hydraulic hand dynamometer (Jamar J00105, Sammons Preston Rolyan, Bolingbrook, USA). The submaximal Åstrand test [35] will be performed on a stationary bicycle ergometer (Examiner, Lode BV, The Netherlands) and the mean heart rate of the last 2 min of the test will be used to estimate the VO_2_max. Heart rate during this test is registered by a heart rate monitor (Polar RS 800, Electro Oy, Finland).

### Questionnaires

At each measurement moment the participant will be asked to fill out a digital questionnaire containing the following instruments:

#### Demographics and personal life events

Socio-demographic data are collected using standard questions on age, sex, marital status, ethnicity and household composition. Socio-economic variables include highest education and income. Personal history is evaluated by the Life Events Questionnaire (LEQ), a 12-item inventory-type questionnaire in which subjects mark the exposure to negative life events such as unemployment, separation from a partner and death of a close family member which have occurred in the past year [36].

#### Mental and physical health and its consequences

The Hamilton Rating Scale of Depression (HRSD) measures depression with a 17-item list performed by trained interviewers [37]., using the Dutch translation of the version of Bech et al. [38], in which the items of depressive symptoms are extensively operationalised and this version is often used in international research [39].

The Inventory of Depressive Symptomatology - Self-Reported (IDS-SR) measures the severity of depression with a 30-item self-report list [40]. It has good responsiveness to change and is more sensitive for atypical depressive criteria than the HRSD. History of depression is evaluated by a single question into the number and duration of depressive episodes for which treatment was necessary.

Bearableness of depression is measured with a visual analogue scale (VAS) ranging from 0 (very unbearable) to 100 (very well bearable). Anxiety is measured by the Beck Anxiety Inventory (BAI), a 21-item multiple-choice self report inventory that measures the severity of generalized anxiety and panic symptoms in adults and adolescents [41].

Pain complaints are evaluated with the Graded Chronic Pain Scale (GCPS) [42], a 7-item scale measuring aspects of pain, physical ability and social interference, resulting in a 5-class hierarchical scale ranging from 0 (no pain problem) to IV (high disability/severely limiting). Next to the GCPS, bearableness of pain is evaluated with a VAS-scale ranging from 0 (very unbearable) to 100 (very well bearable).

Other secondary outcomes are disability during the last 30-days associated with both physical and mental problems and is measured by a shortened version of the World Health Organisation - Disability Assessment Schedule II (WHO-DAS-II) [43], resulting in a disability score ranging from 0-100 with a higher score reflecting greater disability. Quality of life data are collected using the EQ5D [44], a standardized instrument for describing and valuing health related quality of life.

Subjective health is evaluated by a visual analogue scale ranging from 0 (the worst imaginable health condition) to 100 (the best imaginable health condition).

Health care use and work productivity are evaluated by the Trimbos/iMTA Questionnaire for Costs associated with Psychiatric Illness (TIC-P), a 29-item list which focuses on establishing costs related to loss of productivity at work and health care utilization [45].

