**Discussion:**

Exercise in depression can be used as a standalone or as an add-on intervention. In specialised mental health care, chronic forms of depression, co-morbid anxiety or physical complaints and treatment resistance are common. An add-on strategy therefore seems the best choice. This is the first high quality large trial into the effectiveness of exercise as an add-on treatment for depression in adult patients in specialised mental health care.

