A recent meta-analysis of studies into cytokines in depressed patients [25] showed that depression and an *activation of the immune-system *do co-exist. Both tumornecrosisfactor-α (TNF-α) and interleukine-6-concentration (IL-6) were significantly raised and C-reactive protein (CRP) was linearly associated with several conventional risk factors and inflammatory markers [26]. The relevance of CRP however still remains controversial [27]. Therefore, measurement of CRP blood levels in an intervention exercise study could contribute to a better understanding of the clinical importance in relation to heart condition.

The reciprocal relation between *pain and depression *has been reported in several studies where Major Depressive Disorder (MDD) was associated with chronic pain (> 6 months) and nearly 50% of patients had at least one chronic painful physical condition [28,29]. The duration of depressive symptoms was found to be prolonged in the presence of chronic pain. The therapeutic prognosis of co-morbid pain and depression is poor and the pain-depression association was found to be stronger in men than in women and in older adults compared to younger. Productivity was decreased when depression and pain existed in a co-morbid pattern [30].

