### Summarized aims and hypothesis of EFFORT-D

The main objective of the study is to assess the effectiveness of exercise therapy (running therapy (RT) or Nordic walking (NW)), in addition to usual care, on depression in adult patients. We hypothesize that adding exercise therapy to usual care will result in a larger reduction in depressive symptoms (as measured with the Hamilton Rating Scale of Depression, (HRSD)) during a 6 month treatment program as well as at 6 months follow-up, compared to usual care without exercise therapy.

Secondary aims are to assess the effectiveness of exercise therapy (RT or NW) on the following outcome measures: 1) Cardiovascular and metabolic risk parameters as fitness (VO2 max, grip strength), BMI, waist circumference, body composition, blood pressure, fasting blood glucose, cholesterol HDL/LDL ratio and CRP, 2) Co-morbid symptoms of anxiety and pain 3) Quality of life, and 4) Cost-effectiveness.

To assess whether there are subgroups of patients who show a larger or less effect of exercise therapy on depression, subgroup analysis will be conducted differentiated on demographic variables (age, sex) and level and type of depression based on the HRSD, personality traits and level of fitness.

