### Study population

The study population consists of adult patients diagnosed by a clinician with a depression or bipolar disorder with depressive mood, who are or will be treated in GGZ Centraal Mental Hospitals or Symfora-Meander Hospital. Patients aged between 18-65, with a DSM-IV diagnoses of unipolar, bipolar depression or seasonal depression not responding to light therapy (10 sessions of 1 h), a baseline Hamilton Rating Scale of Depression (HRSD) score ≥14 and (will be) treated for depression, are included.

Criteria for exclusion are: a depression as part of a psychotic disorder, schizophrenia, schizoaffective disorder or obsessive compulsive disorder, anxiety disorder as primary diagnosis, patients in long stay facilities (including day-care) or with complex pathology and treatment resistant depression (inpatients, treated by protocol more than 6 months with no remission); patients with significant cardiovascular disease or other medical conditions as contra-indication for exercise therapy, walking and/or running such as joint and hip pathology; alcohol/drugs dependence as a primary diagnosis, pregnancy, high suicide risk with treatment on a closed ward, or already being physically active on a regular basis (2-3 times a week on a high-intensity).

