### Statistical analyses

Comparability of the intervention and control groups will be examined for the baseline measurements. If necessary, analyses will be adjusted for baseline differences. The primary analysis of the data set will be according to the 'intention to treat' principle. A secondary 'per protocol' analysis will be done taking into account the level of compliance and the amount of exercise during the intervention period. Usual daily physical activity, tobacco smoking and alcohol intake will be treated as confounders.

Differences in remission rates (and other categorical outcomes) between the experimental groups are examined by contingency table Chi-square statistics. Differences in mean scores on continuous outcomes (e.g. HRSD) between the intervention groups are examined by analysis-of-variance.

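### The five ordered pain grades fall under a Chi-square rule that ignores both their order and each patient's baseline grade; an ordinal comparison adjusted for baseline would use the same data better

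*Protocol article*

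**What the plan says.** The Summarized aims section lists among the secondary aims "Co-morbid symptoms of anxiety and pain". Under Mental and physical health and its consequences, pain complaints are measured with the GCPS, "resulting in a 5-class hierarchical scale ranging from 0 (no pain problem) to IV (high disability/severely limiting". The same section adds a second, continuous measure: "bearableness of pain is evaluated with a VAS-scale ranging from 0 (very unbearable) to 100 (very well bearable". Table 1 schedules both at T0, T3, T6 and T12, so a baseline grade is recorded for the trial's patients.

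The Statistical analyses section gives two rules for comparing the arms. The one for categorical data reads "Differences in remission rates (and other categorical outcomes) between the experimental groups are examined by contingency table Chi-square statistics". Means of continuous outcomes go to analysis of variance. The section does not name the GCPS and mentions no method for ordered categories. The inclusion criteria in Study population do not mention pain. No section gives an expected distribution of GCPS grades.

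**The concern.** A five-class ordered scale is categorical, so a reader who applies the stated rules sends it to a 2 x 5 table with (2 - 1) x (5 - 1) = 4 degrees of freedom. That test spreads its sensitivity over every possible pattern of difference, although the aim asks about one pattern: a shift towards lower grades. It also takes the follow-up grades alone. A patient who was at grade 0 throughout then counts like one who fell from grade II to 0.

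Because patients are enrolled without regard to pain, some will start at grade 0, where they can only stay or worsen. The larger that share, the more the between-patient spread at follow-up reflects where patients began, and the more is lost by leaving the baseline grade out. What is at stake is a missed pain benefit on a secondary outcome. The false-positive rate and the primary depression result are not affected.

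**Working it through.** **The plan's own figure.** The article states no sample size or power for pain. Its only calculation is for the HRSD: difference 2, SD 5, two-sided 5%, power 80%. Per arm, 2 x (1.960 + 0.842)² x 5² / 2² = 2 x 7.849 x 6.25 = 98.1, or 99 with the t-distribution, against 100 stated. With 30% drop-out, 100 / 0.70 = 143 against 140 stated, and 140 x 0.70 = 98 analysed. These figures reproduce closely enough. They fix the number available for pain at about 100 per arm.

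**Step 1: cost of ignoring order.** Take a shift that a 1-degree-of-freedom ordered test detects with 80% power, so its noncentrality is 7.849. If the effect is purely a trend, the 4-degree-of-freedom Chi-square has the same noncentrality but a critical value of 9.488 instead of 3.841. Its power is 59.5%, a loss of about 20 points. Under proportional odds, with 98 per arm and half of the control arm at grade 0 (grades I to IV assumed to split 35/30/20/15%), Chi-square against ordered test gives:
- odds ratio 1.5: 18% against 32%
- odds ratio 2.0: 48% against 69%
- odds ratio 2.5: 72% against 89%

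**Step 2: order and baseline grade together.** The documents give none of these inputs, so all are assumptions:
- 100 analysed per arm
- a share f at grade 0 at baseline, of whom 90% stay at 0 and the rest move to grade I, in both arms
- control patients with baseline pain end at grades 0 to IV in proportions 15/34/21/17/13%
- exercise multiplies the odds of a lower grade by 2.0 in patients with baseline pain only

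For grade 0 among patients with baseline pain, the control odds are 0.15 / 0.85 = 0.176. Doubled, they are 0.353, a proportion of 0.353 / 1.353 = 0.261. Over the whole arm the difference at grade 0 is (1 - f) x (0.261 - 0.150): 0.9 x 0.111 = 0.100 at f = 10%, and 0.5 x 0.111 = 0.056 at f = 50%.

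Simulated power, all patients analysed:

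| Share at grade 0 at baseline | Chi-square, 4 df | Rank test stratified by floor / non-floor | Gain |
|---|---|---|---|
| 10% | 44% | 71% | 27 points |
| 30% | 27% | 55% | 28 points |
| 50% | 18% | 40% | 22 points |

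Type I error is about 5% for both tests. Repeat runs move these figures by up to about three points.

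**Step 3: which part of the change does the work.** An unstratified rank test in all patients has about 64% power at f = 10% and about 20% at f = 50%. With few patients at the floor, most of the gain comes from using the order (44% to 64%, then 71%). With many at the floor, order alone adds only about 2 points, and nearly all of the gain comes from the baseline grade (20% to 40%). The share is unknown, so the remedy needs both parts.

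**The case against.** **Assignment to the Chi-square is an inference.** The section never names the GCPS, and an analysis plan that is not shown may specify something else. This stands as a caution. The article does, however, state a general rule for categorical outcomes with no exception for ordered ones, so the point concerns what is written and not a detail left out.

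**Baseline is not wholly ignored.** The section allows adjustment for baseline differences where judged necessary. That depends on an observed imbalance between arms. The gain here comes from accounting for each patient's starting grade even when the arms are balanced, and a plain contingency table does not do that.

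**Direction is visible.** A 2 x 5 table displays which way the grades moved. True; the weakness is in the test, not in the display.

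**The pain aim has a second measure.** The bearableness VAS is continuous and falls under analysis of variance, so the aim does not rest on the grade alone. This stands and limits the weight of the point. A reader might suspect that pain-free patients leave the VAS blank and need a scoring rule. Nothing in the article says so, and such a patient can mark the upper end.

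**Pain-free patients dilute a pain effect on any scale.** Correct, so the scale is not at fault. A reader might conclude that patients with baseline pain should be the main population. That would change the question and depart from the stated intention-to-treat analysis, and it would move new-onset pain out of the main result. A contrast of 18% for the Chi-square in all patients with 47% for a rank test in pain patients only changes test and population together, so it does not measure the cost of the Chi-square.

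**Conclusion.** The point holds as a modest improvement to a secondary analysis. On the natural reading of the article, an ordered outcome gets a test that uses neither its order nor its baseline value. Under the assumptions shown, a stratified ordinal test in the same patients gains roughly 22 to 28 points of power at an odds ratio of 2.0, whether 10%, 30% or 50% start at grade 0. The size rests on the assumed grade distribution and odds ratio, and on no effect in patients without baseline pain.

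Two stronger statements are tempting and are not supported. The first is that about half the patients start at the floor. The Background reports that "nearly 50% of patients had at least one chronic painful physical condition", but this is a prevalence of chronic pain in cited studies. Its complement is not GCPS grade 0, because a patient with milder or shorter pain may score above 0. Other text points in both directions: in this setting "co-morbid anxiety or physical complaints and treatment resistance are common", while the exclusion of "other medical conditions as contra-indication for exercise therapy, walking and/or running such as joint and hip pathology" may remove some patients with pain. The second is that most of the power is lost. The unordered test alone takes 80% to about 60%. Heavier losses appear only when the floor share is large, and then mainly through dilution, which an ordinal test without baseline adjustment does not cure.

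**What to change.** In Statistical analyses, except the GCPS from the Chi-square rule and add one sentence: the GCPS grade is compared between arms in all randomised patients with a proportional-odds model adjusted for baseline grade, or with a Wilcoxon test stratified by baseline grade. An analysis restricted to patients with baseline grade I or above may be listed as supportive; that subset is defined before randomisation.

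The cost is wording only. The baseline grade is already collected at T0, and no visit, instrument or patient is added. The proportional-odds model assumes a common odds ratio across grades; the stratified Wilcoxon test is the alternative if that is doubted. If an analysis plan already specifies such a method, the article's rule only needs to be brought into line with it.

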##### Variables expected to modify the effect of the intervention

Personality, as a possible effect modifier, is measured at baseline by the NEO-PI-R, a 60-item validated questionnaire measuring the five domains of personality including neuroticism, extraversion, agreeableness, conscientiousness and openness to experience [46].

##### Confounders: Lifestyle behaviours

Self-reported level of physical activity is assessed by means of the validated Short QUestionnaire to ASsess Health enhancing physical activity (SQUASH), a 12-item questionnaire which evaluates the frequency and duration of physical activities in the domains of work, domestic and leisure time [47]. Tobacco and alcohol intake is measured with a standard single question on the frequency of use per day.

#### Additional measures in the intervention group

The Profile of Mood States (POMS) registers participants' mood after a running session for in total three times during the intervention period (at the beginning, halfway and at the end). The Dutch shortened version of the POMS [48] consists of 32 items divided over seven subscales including tension, depression, anger, fatigue, vigour, positive and negative affect.

At regular intervals participants score their exertion on a Borg-scale ranging from 6 (very, very light) to 20 (very, very severe) [49]. At the end of the intervention period, or when participants dropped out of the RT or NW therapy, a short questionnaire is administered evaluating their satisfaction and experience with the intervention.

### Randomisation, blinding and treatment allocation

Randomisation takes place at every location separately. This way, every location will have an equal distribution of participants between the intervention and control group. The SPSS random generator (SPSS version 14.0) [50] will be used to allocate patients. Ten closed envelopes with allocation numbers are presented to the participants. They choose an envelope, after which the research assistant tells the patients in which arm of the study they are included. Evaluators of the main outcome measure (HRSD) are blinded for group allocation and are trained regularly for inter-rater reliability. All other measures will be evaluated by a research assistant, who is not blinded for group allocation.

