## Discussion

The aim of this study is to investigate the effectiveness of aerobic exercise therapy (RT or NW) on depression in adult patients in addition to usual care. Also, the effect of physical exercise on frequently existing co-morbid diseases or risk factors for such disorders as metabolic syndrome is an objective of this study.

This is the first well conducted add-on randomised controlled high-quality trial into the effect of aerobic exercise on depression with a correct randomisation procedure, blinded outcome assessment, intention to treat analysis, study into cost-effectiveness, quality of life and long-term follow-up as was advised in earlier publications. EFFORT-D can therefore contribute to stronger evidence for this type of intervention, which can result in more specified recommendations for clinical practice. Another strength of this study is the fact that also severely clinically depressed patients, who are mostly excluded in other studies, will be included. A relatively greater effect of exercise in this subgroup of severely depressed patients is possible. A challenge of the study lies in the motivational techniques needed to exercise with depressed patients, which is proven to be difficult [52] and it will take a serious effort not to exceed the calculated 30% drop-out patients in the intervention group. Because this study is supported by a strong hypothesis and minimal negative side effects are expected, one-tailed statistical analysis is also possible if the large number of included participants can't be reached within the planned time. Furthermore, the diversity of outcome measures makes it possible to distinguish more explicitly those depressed patients that could benefit most from exercise.

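### The ten-envelope draw does not by itself give equal arms per location, and if the set is balanced and used up, later allocations become predictable to the research assistant

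*Protocol article*

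**What the plan says.** The section *Randomisation, blinding and treatment allocation* of the protocol article sets out the procedure in these steps:

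- Unit: "Randomisation takes place at every location separately".
- Claimed result: "This way, every location will have an equal distribution of participants between the intervention and control group".
- Generator: "The SPSS random generator (SPSS version 14.0) [50] will be used to allocate patients".
- Draw: "Ten closed envelopes with allocation numbers are presented to the participants".
- Disclosure: "They choose an envelope, after which the research assistant tells the patients in which arm of the study they are included".
- Blinding of staff other than the HRSD raters: "All other measures will be evaluated by a research assistant, who is not blinded for group allocation".

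*Procedures and study instruments* says that the diagnosing psychiatrists pass names of eligible patients to the research assistant, "who will make a first check on inclusion and exclusion criteria, informs the participants and asks them to join the study". It places the cycling test, physical measures and questionnaire before randomisation. Table 1 assigns the HRSD at T0 to a blind rater.

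The section on scientific evidence lists missing concealment among the weaknesses of earlier trials and says that the recommendations of the meta-analyses it cites are built into this design. The Discussion describes the trial as one "with a correct randomisation procedure".

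**The concern.** The text presents equal arms per location as a consequence of randomising each location separately. It is not one. Stratifying by location keeps the sequences apart; balance within a location comes only from a restriction such as blocking. The one feature that could supply a restriction is the set of ten envelopes, and whether it does depends on its composition and refill rule, which are not stated.

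The two obvious ways of running the draw fail differently. A balanced set that is used up gives balance, but it is a fixed block of ten whose remaining contents can be worked out by anyone who hears each arm announced. A set that is replaced, or filled by simple randomisation, cannot be worked out, but it does not secure the balance claimed.

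The first case matters because the person who announces the arm appears to hold the same role that checks eligibility and invites patients. Someone who expects the next allocation to be control, say, can delay or hurry an invitation, or read a borderline exclusion criterion one way or the other. Several criteria under *Study population* leave room for judgement, such as complexity of pathology or being regularly active already. Blinded HRSD rating does not protect against this, because the selection happens before randomisation.

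**Working it through.** **The plan's own figures.** The document gives no figure for predictability or imbalance. The only related figure is the sample size: a difference of 2 points, SD 5, two-sided 5%, 80% power. This gives 2 × (1.96 + 0.84)² × 5² / 2² ≈ 98, or 99 per arm with unrounded quantiles and rounding up, against 100 stated. Dropout of 30% gives 99/0.7 ≈ 142 or 100/0.7 ≈ 143, against 140 stated. The size is reproduced closely enough and is not at issue; it supplies only the planned total of 2 × 140 = 280.

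**Reading A: five envelopes per arm, drawn without replacement until empty (assumed).** Let m = 5 be the number per arm.

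Allocation k is certain in advance when all five envelopes of one arm have gone in the first k − 1 draws. The probability is 2 × C(5, k − 6) / C(10, k − 1):

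| Allocation in the set | Probability that it is certain in advance |
|---|---|
| 6th | 2 × 1/252 = 0.008 |
| 7th | 2 × 5/210 = 0.048 |
| 8th | 2 × 10/120 = 0.167 |
| 9th | 2 × 10/45 = 0.444 |
| 10th | 2 × 5/10 = 1.000 |

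The sum is 1.67, which agrees with 2m/(m + 1) = 10/6. If every set were completed, that is 280 × 1.67/10 ≈ 47 of the planned patients.

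An observer who always guesses the arm with more envelopes left is right on average m + (2^(2m)/C(2m, m) − 1)/2 = 5 + (1024/252 − 1)/2 = 6.53 times in ten, against 5 by chance.

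**Reading B: a balanced set with envelopes returned, or sets filled by simple randomisation (assumed).** Earlier draws carry no information about the next one. The number in one arm among n patients at a location is Binomial(n, 0.5), and the chance of a 60:40 split or worse is 2 × P(X ≥ 0.6n). The document gives neither the number nor the size of locations, so the sizes below are assumptions that span a range:

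| Patients at the location | Exactly equal arms | Mean absolute difference between arms (patients) | 60:40 or worse |
|---|---|---|---|
| 20 | 0.18 | 3.5 | 0.50 |
| 40 | 0.13 | 5.0 | 0.27 |
| 70 | 0.10 | 6.7 | 0.12 |
| 140 | 0.07 | 9.4 | 0.02 |

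**Who could use the information.** Side by side, *Procedures and study instruments* gives the research assistant the first check and the invitation, and *Randomisation, blinding and treatment allocation* has the research assistant announce each arm. No separation between the two tasks is described. Numbering the envelopes in code does not help under Reading A, because the arm becomes known after every draw.

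**The case against.** The best reply is that this is a condensed article. The make-up of the ten envelopes, the refill rule and who prepares them may all be in the full protocol. That is fair, and it means neither reading can be asserted. Nor are the two readings exhaustive: ten envelopes topped up from a larger balanced pool at each location would give balance with little predictability until the end. Nothing in the text describes such a pool, but nothing excludes it. And if equal distribution means only roughly equal, Reading B is a mild fault of wording, especially at large locations.

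The scope for selection is also narrower than it first looks. Psychiatrists supply the names, a blind rater does the T0 HRSD on which the threshold of 14 depends, and baseline is finished before randomisation. There may be several research assistants.

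A reader might infer more than the document supports in three ways:

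- That the recruiter can foresee allocations. This holds only under Reading A.
- That the research assistant also obtains consent. The article puts consent in the passive and names nobody.
- That no sequence exists to audit. The envelopes carry allocation numbers and a generator is named, so a retained list is possible.

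What stands is the stated procedure itself. The patient chooses among envelopes, an unblinded assistant announces the result, no roles are separated, and the claim of equal arms is attached to a step that does not deliver it.

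**Conclusion.** The point holds in conditional form. Randomising each location separately does not by itself yield equal arms, so the claim is unsupported as written.

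If the set is five and five and is used up, 1.67 of every 10 allocations are certain in advance and 6.53 of 10 can be guessed, which opens the way to selective or timed enrolment if recruiter and announcer are the same person. The document suggests that overlap but does not state it. If the set is replaced or filled by simple randomisation, predictability disappears, and the chance of a 60:40 split or worse runs from about 0.50 at 20 patients per location to 0.02 at 140, on assumed sizes.

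It would go too far to conclude that concealment has failed, or that one of these two faults must be present. The procedure should be changed all the same, because this protocol faults earlier trials on concealment and calls its own procedure correct, and the described draw does not support that.

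**What to change.** Drop the step in which patients choose an envelope. Use a computer-generated list for each location, with block sizes varied at random and not disclosed to the research assistant. Have it prepared by someone outside recruitment. Issue allocations strictly in order once the patient is registered, by central release or by sequentially numbered, opaque, sealed envelopes. Keep the existing rule that baseline is completed before randomisation.

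The cost is minor logistics and a short change to the text, with no extra patients or visits. Incomplete last blocks may leave a slight imbalance at a location.

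If the envelope draw is kept, state the composition of the set and the refill rule, and withdraw the claim of equal distribution unless those rules deliver it. That repairs the wording only: a balanced set that is used up would remain predictable.
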